## Abstract

The progressive nature of heart failure (HF) coupled with high mortality and poor quality-of-life (QoL) mandates greater attention to palliative care (PC) as a routine component of HF management. Limited evidence exists from randomized controlled trials supporting the use of interdisciplinary palliative care in the progressive course of HF. The early palliative care in heart failure trial (EPCHF) is a prospective, controlled, nonblinded, multicenter study of an interdisciplinary palliative care intervention in 200 patients with symptomatic HF characterized by NYHA ≥ 2. The 12-month EPCHF intervention includes monthly consultations by a palliative care team focusing on physical and psychosocial symptom relief, attention to spiritual concerns and advance care planning. The primary endpoint is evaluated by health-related QoL questionnaires after 12 months of treatment. First the functional assessment of chronic illness therapy palliative care (FACIT-Pal) score evaluating QoL living with a chronic disease and second the Kansas City cardiomyopathy questionnaire (KCCQ) measuring QoL living with heart failure will be determined. Secondary endpoints are changes in anxiety/depression (HADS), symptom burden score (MIDOS), spiritual well-being functional assessment of chronic illness therapy spiritual well-being scale (FACIT-Sp), medical resource and cost assessment. EPCHF will help evaluate the efficacy and cost-effectiveness of palliative care in symptomatic HF using a patient-centered outcome as well as clinical and economic endpoints. EPCHF is funded by the Bundesministerium für Bildung und Forschung (BMBF, 01GY17).

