We hypothesized that patients who received early PC in the ambulatory care setting, as compared with patients who received standard cardiac care alone, would have a better QoL due to lower rates of depressive symptoms, symptom burden, unmet spiritual needs, reported cardiac outcomes and less aggressive end-of-life care thereby improving QoL for both, patients and their caregivers.

Despite consensus-panel and guideline recommendations the integration of PC with evidence-based HF therapies in the later stages of disease is limited [9, 10]. Many physicians equate PC with end-of-life care and prognostic uncertainty poses a challenge in choosing the appropriate time point to implement PC. Furthermore, cardiologists typically lack formalized training in the PC-principles and it is less clear which HF patients benefit from palliative interventions and which interventions improve QoL achieving outcomes desired by patients and family members [9]. However, multiple recent pilot studies in HF populations have suggested that PC may reduce symptom burden and improve QoL [11–13]. These studies have highlighted the importance of symptoms, such as anxiety and depression in HF patients in addition to the commonly recognized symptoms of fatigue, dyspnea and nausea. Moreover, a randomized trial of PC in Stage 4 lung cancer showed improved patient’s symptoms, improves QoL and patients randomized to PC survived longer than those randomized to usual care [14]. Furthermore, multiple studies in oncology and noncancer illness patients have shown reduced costs leading to increased interest of whether similar results can be found in other common diseases, such as HF [15–17]. These studies provide the foundation and rationale for a large-scale randomized HF trial sufficiently powered to assess the effect of early palliative care on clinical outcomes in HF patients.

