## Methods

### Trial design

EPCHF is a prospective, controlled, two-arm, non-blinded, randomized, multicenter clinical trial of early palliative care integrated with standard cardiac care, as compared with standard cardiac care alone (Fig. 1). The multicenter study will be performed at the departments of Internal Medicine and Palliative Care of the University Hospital of Bonn and departments of Internal Medicine and Palliative Care of the University Hospital of Düsseldorf. Eligible patients with symptomatic HF and dyspnea NYHA ≥ 2 will be randomly assigned to one of the two groups in a 1:1 ratio to usual contemporary HF care or usual care combined with the EPCHF intervention (Fig. 1). Subjects are assigned treatment using a complete randomization scheme. Patients who are assigned to early PC will meet with a member of the PC team, which consisted of board-certified PC physicians and advanced-practice nurses within the time of hospitalization after enrollment and at least monthly thereafter in the outpatient setting during the 12 months of follow-up (Figs. 2 and 3). The palliative care intervention focuses on symptom relief, attention to spiritual concerns, and advance care planning. The trial is non-blinded, since it is not possible to execute a double-blinded trial of the EPCHF intervention given that the intervention involves a multidisciplinary team. The duration of the intervention is 12 months, but patients in both groups are followed until death or the end of the study (~ 3.5 years). The primary endpoint refers to health-related QoL after 12-month follow-up (Fig. 3).

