### Measurements

The primary end point is evaluated by health-related quality-of-life questionnaires after 12 months of treatment (Fig. 3). First, the functional assessment of chronic illness therapy palliative care (FACIT-Pal) score evaluating QoL living with a chronic disease and second the Kansas City Cardiomyopathy Questionnaire (KCCQ) measuring QoL living with heart failure will be determined. The FACIT-Pal is a 14-item measure of self-reported QoL that assesses several domains including physical wellbeing, social/family well-being, emotional well-being, and functional well-being [29]. KCCQ is a 23-item, disease-specific questionnaire scored from 0 to 100 with higher scores representing better health status [30]. A 5-point change in the KCCQ overall summary score has been demonstrated to be the minimally detectable clinical difference [26, 28–34].

Secondary end points are changes in anxiety/depression (HADS), symptom burden score (MIDOS), spiritual well-being Functional Assessment of Chronic Illness Therapy Spiritual Well-Being Scale (FACIT-Sp), medical resource and cost assessment, and a composite of death, HF hospitalization, and quality of life.

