### Data collection

Participants complete baseline questionnaires before randomization. A complete schedule of assessments is given in Fig. 3. Follow-up evaluations of QoL and mood are expected to occur at 3 months, 6 months, 9 months and 12 months. As necessary, we will mail questionnaires to subjects and/or complete questionnaires over the telephone to help ensure the collection of primary endpoint data. When responses on questionnaires were incomplete, research staff documented the reasons for which the participant did not give a full response.

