### Statistical analysis

Primary endpoints: the two primary endpoints will be tested in a two-step procedure. In the first step the hypothesis of equal scores for the FACIT-Pal in the two treatment groups will be tested with a two-side *t* test at a level of 5%. In case of the rejection of the null-hypothesis in the first step, the second hypothesis of equal KCCQ-scores in the two treatment groups will be tested again with a two-sided *t* test at the level of 5%. This test procedure controls a family wise error rate of 5%.

A comparably high number of drop-outs (~ 20%) especially due deaths are to be expected. Since this kind of censoring is definitely correlated to the QoL-measurement, the results for the QoL-score might be biased. An optimal choice of a procedure for the replacement of missing values would require a detailed knowledge about this correlation, which is not available. Missing values will not be replaced for the primary analysis of the two primary outcome variables. A sensitivity analysis will be performed replacing missing values by the last observation carried forward method.

For both variables the course of QoL scores over the observational time will analyzed descriptively by fitting mixed linear models to the data. 95%-confidence interval will be estimated for the score values separated by treatment groups and for measurement times. A second identical analysis for the primary endpoint will be performed based on the per-protocol population (PP), which is defined as the patients treated and observed according to protocol. This analysis will only be performed if ITT and PP-population differ.

Secondary endpoints: the secondary endpoints will be analyzed descriptively in the intention-to-treat collective.

Psychosocial symptoms: patients are screened for symptoms of anxiety and depression using the Hospital Anxiety and Depression Scale (HADS). The HADS has been widely used in studies as a psychologic screening test for the states of anxiety and depression. Patients who screen positive for either anxiety or depression receive a more thorough assessment and management as specified by a treatment algorithm used to determine the need for a mental health referral and the possible use of antidepressants, anxiolytics, stress management techniques, and psychotherapy.

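### LOCF, the one named sensitivity analysis for missing quality-of-life scores, gives patients who died a month-12 score and is a weak check on death-related missingness

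*Protocol article*

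**What the plan says.** All references are to the Protocol article.

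- **Endpoint and visits.** Under Trial design, "The primary endpoint refers to health-related QoL after 12-month follow-up". Under Data collection, "Follow-up evaluations of QoL and mood are expected to occur at 3 months, 6 months, 9 months and 12 months", with a baseline questionnaire before randomisation.
- **Expected missingness.** Statistical analysis puts drop-out at about 20% and gives the main cause: "especially due deaths are to be expected". It is firm that this censoring is related to QoL, warns of bias, and says the strength of the relation is not known.
- **Handling.** Missing values are not replaced in the primary t tests of FACIT-Pal and KCCQ. Then: "A sensitivity analysis will be performed replacing missing values by the last observation carried forward method". No separate rule is given for patients who died.
- **Other analyses nearby.** Mixed linear models describe the course of both primary scores. A per-protocol repeat follows if the populations differ. Survival is compared by log-rank test and Cox models. Measurements lists, among the secondary endpoints, "a composite of death, HF hospitalization, and quality of life"; secondary endpoints are analysed descriptively by intention to treat, with further detail left to a statistical analysis plan.

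**The concern.** The article names the problem and then fixes a check that does not fit it well. When the link between drop-out and QoL is unknown, a sensitivity analysis should vary that link. LOCF makes a single assumption: nothing changes after the last questionnaire. The article describes heart failure as progressive with high mortality. For a patient who died, LOCF also supplies a living score at a time when no score exists. Death is never counted as an outcome, and the carried-forward values enter the t test as if they had been observed.

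At stake is how the QoL result is interpreted. If observed-case and LOCF results agree, readers may take the finding as robust to deaths when neither analysis has brought death into the comparison. An unequal split of deaths is not far-fetched in this trial's own terms. The Background cites a Stage 4 lung cancer trial in which "patients randomized to PC survived longer than those randomized to usual care", and the plan itself tests survival by arm. That citation concerns another disease and says nothing about the size or direction of any effect in heart failure.

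**Working it through.** **Figures the article gives.** The Abstract describes a "palliative care intervention in 200 patients with symptomatic HF", and Trial design says they are "randomly assigned to one of the two groups in a 1:1 ratio", so about 100 per arm. Drop-out is about 20%. Hence 0.20 × 200 = 40 patients without a month-12 score and 160 with one, about 80 per arm if equal. KCCQ runs from 0 to 100, with 5 points as the yardstick. The article gives no deaths per arm, SD, effect size or power, so there is no stated figure on this point to reproduce.

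**Assumed inputs.** All missing scores are deaths. Mean of survivors S = 65 KCCQ points in both arms. Mean last score before death L = 40 to 50. Death proportions are d_T (early palliative care) and d_C (control), averaging 20%.

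**Formulas for the difference, T minus C.**
- Observed cases: S − S = 0.
- LOCF: [(1 − d_T)S + d_T·L] − [(1 − d_C)S + d_C·L] = (d_C − d_T)(S − L).
- Death scored 0: (1 − d_T)S − (1 − d_C)S = (d_C − d_T)S.

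**Worked case, 15% v 25%.**
- LOCF, L = 50: 0.10 × 15 = 1.5.
- LOCF, L = 40: 0.10 × 25 = 2.5.
- Death scored 0: 0.10 × 65 = 6.5.

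| Deaths T v C | Observed cases | LOCF (L = 50 to 40) | Death scored 0 |
|---|---|---|---|
| 20% v 20% | 0 | 0 | 0 |
| 15% v 25% | 0 | 1.5 to 2.5 | 6.5 |
| 25% v 15% | 0 | −1.5 to −2.5 | −6.5 |
| 10% v 30% | 0 | 3.0 to 5.0 | 13.0 |

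LOCF moves in the right direction, but by (S − L)/S of the death-inclusive shift: 15/65 = 23% to 25/65 = 38%. Scoring death as 0 is a convention, used here only to show scale; a rank analysis avoids choosing a number.

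**Simulation.** 4,000 trials per scenario, 100 per arm, assumed SD 20, death more likely at low QoL, last visit at month 0, 3, 6 or 9, and no underlying decline in scores. Percentage of trials significant at two-sided 5%:

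| Scenario (deaths T v C; true QoL gain) | Observed cases | LOCF | Rank, deaths below all survivors |
|---|---|---|---|
| 20% v 20%; none | 5% | 5% | 4% |
| 15% v 25%; none | 6% | 6% | 17% |
| 25% v 15%; 8 points | 83% | 65% | 13% |

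In the last row the two QoL analyses usually agree on a benefit in a trial with excess deaths in the intervention arm. The rank analysis seldom does, because the gain and the deaths offset each other. These analyses answer different questions. The table shows only that agreement between the first two says little about the third.

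**The case against.** **LOCF is not blind to deterioration.** A reader might infer that LOCF cannot test the feared bias at all. That goes too far. It uses the low scores of patients who later died. In the simulation with no QoL effect and stable scores, it removed a survivor-selection bias of about 1 point (deaths 15% v 25%) to 2 points (10% v 30%). What remains is that it holds one assumption fixed and never counts death.

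**Other analyses exist.** A reader might infer that a survival effect would go unseen. The documents do not support this: log-rank and Cox analyses compare survival directly, and the monitoring board can stop for harm. The mixed models also use the interim scores of patients who drop out, under a different assumption from LOCF. But the models are descriptive and extrapolate past death, the per-protocol repeat changes the population rather than the missing-data assumption, and the survival analyses stand beside the QoL comparison rather than inside it.

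**The composite.** It might seem that the composite containing death has no analysis. It has a descriptive intention-to-treat analysis, and its detail is properly left to the analysis plan. It is not offered as a check on the primary QoL comparison.

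**False precision.** Counting 200 values instead of 160 suggests a standard error smaller by 11% (√(160/200) = 0.894). That holds only if the SD is unchanged. With SD 20, 20% imputed and last scores 15 to 25 points lower, the SD becomes √(400 + 0.16 × 225) = 20.9 to √(400 + 0.16 × 625) = 22.4. The ratio is then 0.93 to 1.00, a reduction of 0 to 7%, so this is a minor issue.

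**Scope.** LOCF is only a sensitivity analysis. It does not affect the primary test, the error rate or the sample size. This stands and limits the severity.

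**Conclusion.** The point holds as a cheap improvement that should be made, not as a flaw in the primary test. The article itself fixes LOCF, without an exception for deaths, directly after describing drop-out that is driven by deaths and related to QoL. This is a weak method that has been stated, not a detail left to the analysis plan. Agreement between observed-case and LOCF results would be weak evidence of robustness to death-related missingness.

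The size is conditional. A 10-percentage-point imbalance in deaths under the assumptions above leaves LOCF below the 5-point KCCQ yardstick (1.5 to 2.5), while a comparison with death scored 0 exceeds it (6.5). The split of deaths, the mean scores and the SD are assumptions; the article gives none of them. With equal deaths and equal QoL loss in both arms, nothing changes. For FACIT-Pal, the first endpoint in the sequence, the reasoning is the same, but the article gives no yardstick against which to set a figure.

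**What to change.** Keep the primary tests as they are. In the analysis plan, before any outcome comparison by arm:

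1. State how death enters the month-12 QoL comparison.
2. Replace or supplement LOCF with a month-12 comparison of all randomised patients that counts death as the worst outcome, for example a rank-based analysis, for FACIT-Pal and again for KCCQ. Other death-inclusive or survivor-based definitions are defensible; what matters is choosing one in advance.
3. For living patients with missing scores, use multiple imputation with a delta shift applied by arm and increased until the conclusion changes (tipping point).
4. Show deaths and other missing scores by arm beside the primary result.

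The cost is a few lines in the plan and some programming. No new data are needed: both arms are already to be followed until death or study end, and reasons for incomplete questionnaires are recorded. The drawback is that a rank result is harder to interpret than a mean difference, which is a reason to keep it as a sensitivity analysis.

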### Trial organization

A Data and Safety Monitoring Board (DSMB) has been appointed to review the conduct and results of this trial at 2 enrollment landmarks (after 33% and 66% of the patients have been enrolled). The DSMB is charged with reviewing safety composite data in both arms of the trial. The DSMB will be empowered to stop the study for evidence of harm, but not for evidence of lack of efficacy. The DSMB is also asked to offer perspective on any therapeutic or diagnostic testing advances that may occur during the trial course that may influence the outcome. If protocol modifications are warranted, close consultation among the DSMB and the study leadership will be required.

## Summary

HF creates significant physical, psychosocial and spiritual burden for patients and their families. Palliative care may represent an important component of the holistic management of patients with not only advanced HF. Further evidence from randomized trials of a palliative care intervention in HF is required to identify which patients may benefit from specific interventions. EPCHF aims to provide empiric data to support the efficacy and cost-effectiveness of palliative care improving the health-related QoL in HF patients after hospitalization. Such evidence could provide impetus to overcome current challenges related to limited access to, and adoption of, palliative care services for HF patients.

## Abbreviations

BMBF: Bundesministerium für Bildung und Forschung
BNP: B-type natriuretic peptide
EPCHF: Early palliative care in heart failure trial
FACIT-Pal: Functional assessment of chronic illness therapy palliative care
FACIT-Sp: Functional assessment of chronic illness therapy spiritual well-being scale
HF: Heart failure
KCCQ: Kansas City cardiomyopathy questionnaire
HADS: Hospital anxiety and depression scale
LVEF: Left ventricular ejection fraction
MIDOS: Minimal documentation system
NT-proBNP: N-terminal pro-B-type natriuretic peptide
NYHA: New York Heart Association
PC: Palliative care
QoL: Quality of life
